### Handling of Missing Data

3.6

Missing data for the primary outcomes are expected to be minimal (< 5%) given the registry‐based follow‐up for mortality and comprehensive hospital records for days alive outside the hospital. The primary analysis will include all participants with available data.

If missing data exceed 5% for primary outcomes and are believed to be missing at random, the following approaches will be used:
Multiple imputation: Missing values will be imputed using chained equations with 50 imputations, incorporating baseline characteristics and treatment allocation to the four interventions, but without including treatment interactions.Best‐worst and worst‐best case scenarios: To assess the potential range of impact of missing data, best‐worst scenarios (all patients with missing data in the intervention group assumed a beneficial outcome; all in the control group assumed a harmful outcome) and worst‐best scenarios (reverse assumptions) will be presented. For numerical outcomes, best, respectively, worst‐case scenarios will be imputed using the minimum, respectively, maximum taken of the numerical outcome over all non‐missing patients.Sensitivity analyses: Additional sensitivity analyses assuming all participants with missing data were either all alive or all dead (for mortality outcomes) will be performed.

For secondary and tertiary outcomes, missing data mechanisms will be evaluated, and multiple imputation will be used if appropriate. Complete case analyses will be reported alongside imputed analyses.

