*There is no difference in 90‐day all‐cause mortality between the dexamethasone and placebo groups*.

*Treatment with dexamethasone leads to improved rates of survival at 90 days compared to placebo*.

*There is no difference in 90‐day all‐cause mortality between backrest elevation at 35° and 5°*.

*An elevated backrest at 35° leads to improved rates of survival at 90 days compared to elevation at 5°*.

*There is no difference in days alive outside of hospital within 30 days between early wakeup (sedation ≤ 6 h) and mandatory sedation (28–36 h)*.

*Mandatory sedation for 28–36 h leads to more days alive outside of the hospital in 30 days compared to sedation for ≤ 6 h*.

*There is no difference in days alive outside of hospital within 30 days between Olanzapine and placebo*.

*Treatment with olanzapine leads to more days alive outside of the hospital in 30 days compared to placebo*.

This statistical analysis plan is one of several companion manuscripts for the DANOHCA trial, each addressing a prespecified intervention within the shared factorial trial framework. Intervention‐specific rationale and procedures are described in four corresponding protocol manuscripts; the present SAP outlines the methodological approach to analyzing the common primary, secondary, and tertiary outcomes of the DANOHCA trial. This predefined plan aims to minimize analytic bias, ensure transparency, and enhance the interpretability of intervention effects on clinically important outcomes.

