#### Primary Outcomes

2.5.1

The trial employs intervention‐specific primary outcomes:
Dexamethasone intervention: All‐cause mortality at 90 days.Backrest elevation intervention: All‐cause mortality at 90 days.Olanzapine intervention: Days alive outside hospital within 30 days.Early wakeup intervention: Days alive outside the hospital within 30 days.

The choice of intervention‐specific primary outcomes reflects the anticipated mechanism of action for each intervention. Dexamethasone and backrest elevation target pathophysiological pathways that may directly affect early survival—dampening systemic inflammation and increasing cerebral perfusion pressure, respectively—thereby making 90‐day all‐cause mortality the most clinically relevant primary endpoint. In contrast, olanzapine and the early wakeup strategy primarily aim to reduce delirium and sedation‐related complications, translating into improved functional recovery and shorter hospital stays rather than a direct effect on mortality. Days alive outside the hospital within 30 days reflect both survival and time to recovery, and are therefore a more sensitive and clinically meaningful primary endpoint for these two interventions.

Days alive outside the hospital within 30 days are calculated by subtracting the time spent in the hospital or deceased within 30 days, then rounding down to the nearest whole number. Thus, a patient dying on admission day has zero days alive outside the hospital, and a patient with hospitalization exceeding 30 days also has zero days alive outside the hospital. A day (≥ 24 h) spent at a hospital or healthcare facility operated by a Danish region counts as time in hospital, whereas outpatient visits and brief hospitalizations < 24 h count as days alive outside hospital.

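### Section 3.6 reverses best and worst case for days alive outside hospital, and ties the extreme-case checks to data believed missing at random

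*SAP article*

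**What the plan says.** Section 3.6 (Handling of Missing Data) expects under 5% missing primary outcome data and analyses the participants who have data. It then sets a condition: "If missing data exceed 5% for primary outcomes and are believed to be missing at random, the following approaches will be used". Three items follow in one list:

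- multiple imputation by chained equations;
- best-worst and worst-best scenarios, whose purpose is given as "To assess the potential range of impact of missing data";
- for mortality, "Additional sensitivity analyses assuming all participants with missing data were either all alive or all dead (for mortality outcomes) will be performed".

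The best-worst scenario is defined as "all patients with missing data in the intervention group assumed a beneficial outcome; all in the control group assumed a harmful outcome", and worst-best is the reverse. For numerical outcomes the text adds that "best, respectively, worst‐case scenarios will be imputed using the minimum, respectively, maximum taken of the numerical outcome over all non‐missing patients".

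The direction of the numerical primary outcome is stated elsewhere. Section 2.5.1 notes that "a patient dying on admission day has zero days alive outside the hospital", and the olanzapine hypothesis in the Background is "Treatment with olanzapine leads to more days alive outside of the hospital in 30 days compared to placebo". Section 4.4 (Methodologic Considerations) presents multiple imputation and the sensitivity analyses as testing robustness across a variety of assumptions about the missing data, and does not mention the condition.

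**The concern.** There are two separate faults in the same section.

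**Direction.** Read in word order, best case means the minimum and worst case the maximum. For days alive outside hospital the minimum, zero, is the value given to a patient who dies on the day of admission. The rule therefore enters the most harmful value where the definition just before it asks for a beneficial one, and a programmer cannot satisfy both sentences. For olanzapine and early wakeup, the scenario labelled favourable to the intervention would be the unfavourable one.

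**Condition.** The extreme-case analyses show how far the result could move if the missing values are not like the observed ones. They are most useful when missing at random is in doubt, yet the plan makes them depend on believing it. Section 3.1 itself allows one route to outcome-related loss: a participant may ask for their data to be deleted, which only a surviving participant can do.

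**Working it through.** **1. The plan's own figures.** Both sample sizes reproduce, so its planning values can be used.

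- Days alive outside hospital: difference 1.5, SD 7, 90% power, two-sided 5%. n per arm = 2 × (1.960 + 1.282)² × 7² / 1.5² = 458, or 916 in total, against the stated 920. With 460 per arm the power is 90.1%.
- Mortality: 35% versus 26%, 85% power. The usual two-proportion formula gives 469 per group, against the stated 468.

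**2. Direction of the numerical rule.** Let m be the missing share in each arm (assumed equal), d the observed mean difference (intervention minus control), and Min and Max the observed extremes. Min is taken as 0. Max is not given in the document; 28 to 30 days is assumed.

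- By the definition (beneficial = Max, harmful = Min): best-worst = (1 − m)d + m(Max − Min), and worst-best = (1 − m)d − m(Max − Min).
- By the literal numerical rule (best = Min, worst = Max) the two expressions change places.

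With m = 0.05:

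- d = 0: best-worst should be +0.05 × 28 = +1.4 to +0.05 × 30 = +1.5 days. The literal rule gives −1.4 to −1.5.
- d = 1.5, Max = 28: 0.95 × 1.5 = 1.425 and 0.05 × 28 = 1.4. Best-worst should be 2.825 and worst-best 0.025. The literal rule reports the same two numbers with the labels exchanged.

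**3. What the condition leaves out.** Section 3.6 gives these cases for primary outcomes:

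- more than 5% missing, believed missing at random: all three items in the list;
- more than 5% missing, not believed missing at random: no item in the list applies;
- 5% or less missing, the case the plan expects: available data only.

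Every sensitivity analysis listed for primary outcomes thus requires belief in missing at random. That does not match the description in Section 4.4.

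**4. Can 5% or less matter?** Take mortality at the planning values, 500 per arm, equal missingness. In worst-best, missing intervention patients count as dead and missing control patients as alive.

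- m = 0.03: intervention 0.97 × 0.26 + 0.03 = 0.2822; control 0.97 × 0.35 = 0.3395; difference −5.73 points. SE = √[(0.2822 × 0.7178 + 0.3395 × 0.6605)/500] = 0.0292; z = −1.96.
- m = 0.05: intervention 0.95 × 0.26 + 0.05 = 0.2970; control 0.95 × 0.35 = 0.3325; difference −3.55 points. SE = √[(0.2970 × 0.7030 + 0.3325 × 0.6675)/500] = 0.0294; z = −1.21.

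For comparison, the complete-case difference is −9.0 points. With 475 per arm observed, SE = √[(0.35 × 0.65 + 0.26 × 0.74)/475] = 0.0297 and z = −3.03. A bound that no longer excludes zero is therefore possible at 5% missing, and 3% is borderline.

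For days alive outside hospital the largest shift from d = 0 is 0.03 × 28 to 0.03 × 30 = 0.84 to 0.90 days at 3% missing, and 1.4 to 1.5 days at 5%, against a design effect of 1.5 days.

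**The case against.** The strongest reply is that little follows from the swap. Both scenarios are presented together, so exchanging minimum and maximum exchanges two labels and leaves the pair of estimates, and the range they span, as they were. That stands. A reader might infer an error of up to 3 days in what is reported (from +1.5 to −1.5). The document does not support this: the 3 days is the distance between two results that would both be shown. The beneficial/harmful definition also makes the intention clear, and a best case lying below the complete-case estimate would probably be noticed. The minimum/maximum wording would suit lower-is-better measures such as length of stay.

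On the condition, analysing available data when little is missing and adding methods above a threshold is a legitimate prespecified choice. Sections 3.6 and 4.4 give the reason: registry and hospital-record follow-up should leave few gaps. So the 5% threshold is not in itself an error. This defence does not reach the second half of the condition. Requiring belief in missing at random is natural for multiple imputation but not for bounds.

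The size figures also have limits. The primary analysis of days alive outside hospital is a Wilcoxon rank-sum test with a median difference (Section 3.2.2). The shifts above are in the mean, which is only supplementary there, and they do not measure the effect on the primary test. Nor does the mortality difference shift by exactly the missing share. At 4.9% missing, the shift would be ±4.9 points only if the observed difference were zero. At the planned 9 points it is 4.9 + 0.049 × 9 = 5.3 in one direction and 4.9 − 0.049 × 9 = 4.5 in the other.

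**Conclusion.** Both faults hold as written. The numerical rule is reversed for the one numerical primary outcome and contradicts the definition beside it; the consequence is exchanged labels for two of the four primary comparisons, with the range unchanged. The extreme-case checks are withheld when more than 5% of data are missing and missing at random is not believed, which is where they are most needed and is at odds with Section 4.4. Not running them at 5% or less is a weaker point, but the figures show that losses of that size could matter.

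The sizes rest on equal missingness per arm, the plan's own mortality assumptions with 500 per arm, and an assumed observed range of 0 to 28–30 days.

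A reader might infer that the primary results are compromised. They are not: no primary estimate, test, sample size or significance level changes, and the plan expects little missing data. This is a correction that should be made, not one on which the validity of the trial turns.

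**What to change.** Two changes to Section 3.6:

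1. State the extremes by direction. For days alive outside hospital, the best case is the maximum observed and the worst case the minimum observed; for numerical outcomes where lower is better, the reverse.
2. Tie only multiple imputation to the missing-at-random assumption. Run best-worst, worst-best and, for mortality, all-alive and all-dead whatever mechanism is believed, and preferably whenever any primary outcome value is missing.

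The cost is two sentences and a few lines of code. If almost nothing is missing, the checks are trivial to run and report. Correcting the text before the analysis also avoids a later departure from the plan that Section 3.12 would require to be documented and justified.

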### Assessment of Statistical Assumptions

3.7

All statistical analyses will undergo a systematic assessment of underlying assumptions [10][11].

#### Assumptions for Regression Models

3.7.1

##### Mixed‐Effects Models

3.7.1.1

For mixed‐effects logistic and linear regression models, the following assumptions will be assessed:
Normality of residuals (linear models): Assessed using quantile‐quantile plots of residuals.Homogeneity of variances (linear models): Assessed by plotting residuals against covariates and fitted values.Random effects structure: Appropriateness of site as a random effect will be assessed using likelihood ratio tests. Normality of random effect estimates will be assessed using quantile‐quantile plots.

If assumptions are violated, appropriate transformations (logarithmic, square root), robust standard errors, or bootstrapping will be considered.

##### Cox Proportional Hazards Models

3.7.1.2

Proportional hazards assumptions will be assessed using:
Schoenfeld residuals plotted over time.Log–log plots of survival curves.Statistical tests of Schoenfeld residuals.

If proportional hazards assumptions are violated, time‐varying coefficients or stratified Cox models will be considered.

##### Proportional Odds Models

3.7.1.3

The proportional odds assumption for ordinal outcomes will be assessed using:
Brant tests for the parallel regression assumption.Graphical assessment of cumulative probabilities.

If assumptions are violated, partial proportional odds models or generalized ordered logit models will be used.

### Safety Analyses

3.8

Adverse events and serious adverse events will be summarized by intervention group using descriptive statistics. The following adverse events will be specifically monitored: major bleeding, infections (pneumonia, sepsis, pyelonephritis, upper airway infections), renal impairment requiring renal replacement therapy, electrolyte disorders, metabolic disorders (hypoglycemia, prolonged hyperglycemia), cardiac events (ventricular fibrillation, ventricular tachycardia, atrial fibrillation requiring cardioversion, new need for pacing, prolonged QT interval > 560 ms, circulatory collapse), respiratory events (auto‐extubation, need for reintubation), seizures (tonic–clonic, myoclonic, status epilepticus), extrapyramidal side effects, skin complications (pressure ulcers, acne, atrophy, purpura, reduced wound healing), and death after withdrawal of life‐sustaining therapy.

Adverse reactions potentially related to specific interventions will be identified:
Dexamethasone: Infections, hyperglycemia, skin complications (acne, atrophy, purpura, reduced wound healing).Olanzapine: Ventricular arrhythmias, prolonged QT interval, bucco‐linguo‐masticatory syndrome.Backrest elevation: Pressure ulcers occurring within 96 h.

Safety outcomes will be analyzed using descriptive statistics and risk ratios with 95% confidence intervals. No formal hypothesis testing will be performed for safety outcomes, but clinically meaningful differences will be highlighted.

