### Inclusion Criteria

2.1

Out‐of‐hospital cardiac arrest of presumed cardiac cause.Age ≥ 18 years.Sustained ROSC (defined as ≥ 20 min without chest compressions or mechanical circulatory support).Unconsciousness (Glasgow Coma Scale < 9, unable to obey verbal commands) upon admission.

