### General Principles

3.1

All analyses will be conducted according to the modified intention‐to‐treat principle, including all randomized participants who meet the inclusion criteria and have available outcome data, or imputed outcome data (see missing data section below). Participants who do not fulfill the inclusion criteria will be excluded from analyses. If consent is subsequently withdrawn, data collected prior to withdrawal will be included in the primary analysis in accordance with the EU Clinical Trials Regulations, unless the participant explicitly requests deletion of their data. A per‐protocol analysis will be performed as a sensitivity analysis, including only participants who received all scheduled doses of pharmacologic interventions, adhered to the assigned backrest position for ≥ 80% of the time, and had a wakeup call attempted within the assigned time frames.

Data will be analyzed and reported as four individual trials, with no adjustment for multiple comparisons planned. This approach is justified because almost all previous trials in the hospital phase of out‐of‐hospital cardiac arrest care have been neutral, and all four interventions are accepted without considering potential interactions. If more than one intervention shows a non‐neutral result, interactions between interventions will be evaluated by including pairwise and higher‐order interaction terms in the primary regression models for each intervention, applying the prespecified thresholds defined in Section 3.5 (interaction *p* < 0.01 and absolute effect ≥ 5.6%). If a clinically important interaction is identified, results for the affected interventions will be presented both as overall estimates and stratified by the interacting intervention allocation. All regression analyses will be adjusted for site as a covariate.

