### Assessment of Interactions Between Interventions

3.5

As a safety measure and to investigate potential synergistic or antagonistic effects, interactions among the four interventions will be assessed with respect to 90‐day mortality, days alive outside the hospital within 30 days, and the occurrence of serious adverse events. Interaction terms will be included in regression models, and interactions will be considered significant if the interaction term has *p* < 0.01 and demonstrates a clinically important effect (based on the anticipated intervention effect used in sample size calculations, i.e., absolute risk reduction of 5.6%).

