### Methodologic Considerations

4.4

The factorial design requires careful attention to potential interactions. If interventions act through independent mechanisms without synergy or antagonism, factorial analysis is efficient and valid. However, if substantial interactions exist, main effects may be misleading. This plan includes rigorous assessment of interactions, with criteria for both statistical significance (*p* < 0.01) and clinical importance (absolute effect ≥ 5.6%) to avoid false‐positive findings. If important interactions are identified, results will be presented with appropriate stratification.

The modified intention‐to‐treat approach balances statistical rigor with clinical pragmatism. Including only participants who meet the inclusion criteria avoids diluting treatment effects from ineligible patients while maintaining randomization integrity. Per‐protocol analyses will provide complementary information about intervention effects under ideal adherence but must be interpreted cautiously given potential selection bias.

Handling of missing data follows current best practices. Registry linkage for mortality ensures complete ascertainment of the primary outcome for Dexamethasone and backrest interventions. Days alive outside the hospital can be ascertained from hospital records and national registries with minimal missingness. Nevertheless, the plan includes multiple imputation and sensitivity analyses to assess the robustness of the findings under different missing‐data assumptions.

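### As worded, the eligibility exclusion in Section 3.1 also removes randomised participants from the safety analyses (minor wording correction)

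*SAP article*

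**What the plan says.** Section 3.1 (General Principles) sets the analysis population for the whole plan: "All analyses will be conducted according to the modified" form of intention to treat. It then adds: "Participants who do not fulfill the inclusion criteria will be excluded from analyses". The one departure it names is the per-protocol sensitivity analysis. Data collected before a withdrawal of consent are kept, "unless the participant explicitly requests deletion of their data".

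Section 3.8 (Safety Analyses) summarises adverse events by intervention group and says: "Safety outcomes will be analyzed using descriptive statistics and risk ratios with 95% confidence intervals". It continues: "No formal hypothesis testing will be performed for safety outcomes, but clinically meaningful differences will be highlighted". It names no population of its own.

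Section 3.5 describes its models for interactions among the four interventions as a safety measure. Their outcomes are 90-day mortality, days alive outside hospital "and the occurrence of serious adverse events".

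Section 4.4 (Methodologic Considerations) gives the reason for the exclusion: "Including only participants who meet the inclusion criteria avoids diluting treatment effects from ineligible patients while maintaining randomization integrity".

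**The concern.** Sections 3.5 and 3.8 both describe analyses, and Section 3.1 speaks of all analyses without exempting safety. Taken at its word, the plan removes from the harms tables and the serious adverse event models any randomised participant found not to meet the inclusion criteria, whether or not that participant was exposed.

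Exposure before the problem is noticed is possible. Both study drugs start as soon as possible after admission (Sections 2.4.1 and 2.4.2), while a criterion such as 20 minutes of sustained circulation could be found unmet on later record review.

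An adverse event in someone who received dexamethasone or olanzapine is evidence about harm whatever is later learned about eligibility. The dilution argument in Section 4.4 does not reach that case. What is at stake is mainly the rare events listed in Section 3.8, where differences are to be highlighted without a formal test and one missing event shows in the table.

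**Working it through.** **Which text governs.**

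- Section 3.1 sits under general principles and covers all analyses. Its exclusion sentence is neither limited to efficacy nor conditional on exposure.
- Section 3.8 reports risk ratios with confidence intervals and defines no denominator.
- The Abstract attaches intention to treat to the primary analyses only and defines no safety population.
- Section 3.6 (missing data) and Section 4.4 contain no exemption for safety.

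Nothing in the document overrides Section 3.1 for harms.

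**Who would be caught.** The exclusion sentence names the inclusion criteria only. Section 2.1 lists four: out-of-hospital "cardiac arrest of presumed cardiac cause", age, sustained return of circulation, and unconsciousness on admission. Most are bedside facts at enrolment, and a presumed cause is not undone by a later diagnosis. The number caught should be small and may be close to zero. The document gives no figure.

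**Inputs.** From Section 2.6: 1000 patients, 500 per arm for each intervention. Assumed, because the document gives neither: 0 to 20 participants excluded, and event risks of 20%, 2% and 1%.

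**Expected events lost over both arms**, at 20 excluded: 20 × 0.20 = 4; 20 × 0.02 = 0.4; 20 × 0.01 = 0.2. The ranges are therefore 0–4, 0–0.4 and 0–0.2.

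**Chance of losing at least one active-arm event**, 1 − (1 − p)^m with m excluded in that arm:

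| Event risk p | m = 10 (20 excluded) | m = 5 (10 excluded) |
|---|---|---|
| 20% | 1 − 0.80^10 = 0.893 | 1 − 0.80^5 = 0.672 |
| 2% | 1 − 0.98^10 = 0.183 | 1 − 0.98^5 = 0.096 |
| 1% | 1 − 0.99^10 = 0.096 | 1 − 0.99^5 = 0.049 |

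**Effect on the risk ratio.** This was simulated with 400,000 trials, 500 per arm, equal true risks, and exclusions split at random between arms and unrelated to outcome. Trials with no remaining events in an arm (under 1.5%) were omitted. The ratio of the risk ratio after exclusion to that before has geometric mean 1.00 at 5, 10 and 20 excluded, for all three risks. At 20 excluded:

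| Event risk | Middle 95% of after/before ratio | 95% CI of the risk ratio itself (equal events per arm) | Chance that only the active arm loses an event |
|---|---|---|---|
| 20% | 0.965–1.037 | 0.78–1.28 (100 v 100) | 0.110 |
| 2% | 0.857–1.167 | 0.42–2.38 (10 v 10) | 0.151 |
| 1% | 0.759–1.317 | 0.29–3.43 (5 v 5) | 0.087 |

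The confidence intervals are Wald intervals on the log scale. For 10 v 10 events, the standard error is √(1/10 − 1/500 + 1/10 − 1/500) = 0.443, and exp(±1.96 × 0.443) gives 0.42–2.38.

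**Extremes**, dropping one active-arm event and nothing else:

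- 20% risk: (99/499)/(100/500) = 0.992
- 2% risk: (9/499)/(10/500) = 0.902, 95% CI 0.37–2.20
- 1% risk: (4/499)/(5/500) = 0.802, 95% CI 0.22–2.97

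**Precision.** With 490 instead of 500 per arm, the standard error of the log risk ratio rises by √(500/490) − 1 = 1.0%.

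**The case against.** The strongest reply is that the rule was never meant for safety. The sentence in Section 3.1 defines the set partly by observed or imputed outcome data, and imputation has no place in adverse event listings. Section 4.4 speaks only of treatment effects. An article that defers detail to four protocol papers may fairly leave a safety population to the protocol. This reading of the intent is plausible, but the text does not state it. The document is not merely silent, because it fixes a population for all analyses. A different safety set in the protocol would conflict with this text and would not cure it.

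It can also be said that almost nobody is affected, that no direction of bias is shown, and that safety is descriptive and separately overseen by a data-monitoring committee. All of that stands, and it is why the point is minor.

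Finally, the correction gives the serious adverse event models in Section 3.5 a slightly different population from the mortality models beside them, and all-randomised is a broader set than all-exposed. The first is a trivial cost. On the second, keeping everyone in the allocated group preserves the randomised comparison and still retains every exposed participant.

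**Conclusion.** The point holds as a minor wording correction. As written, Section 3.1 removes randomised participants found not to meet the inclusion criteria from the analyses in Section 3.8 and from the serious adverse event models in Section 3.5, for a reason that concerns efficacy only.

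The consequence is probably very small. Even at the assumed upper limit of 20 exclusions, the middle 95% of shifts in a risk ratio stays well inside that ratio's own confidence interval. Shifts to about 0.90 at 2% risk or 0.80 at 1% need a whole event lost in one arm only, which has a chance of about 15% and 9% at that upper limit. These figures rest on assumed exclusion counts and event risks, and on exclusions being unrelated to allocation and outcome. No systematic distortion of the safety conclusions is claimed.

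**What to change.** In Section 3.1, limit the exclusion: *Participants found not to meet the inclusion criteria are left out of efficacy analyses; this exclusion does not apply to safety analyses.*

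In Section 3.8, add: *Safety analyses for each intervention, including the serious adverse event models in Section 3.5, include all randomised participants by allocated group regardless of later findings on eligibility, except those who explicitly ask for their data to be deleted.*

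The cost is two sentences. The adverse event data are already collected, no patients or procedures are added, and the modified intention-to-treat set for efficacy can stay as it is. Safety tables may carry a slightly larger denominator than the efficacy tables, which a footnote can explain.
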